## Abstract

**Background:**

Obesity has become a major public health problem. Innovative treatments are necessary. Internet and new technologies have been reported effective results in weight control programs, especially those with personalized feedback. This paper presents the protocol for a randomized controlled trial to test the effectiveness of an online weight control program, called *en_línea,* comparing with a standard group therapy and a control group.

**Methods:**

This is a randomized controlled trial with three intervention arms: *en_línea,* standard group therapy and control group. To perform this study, 305 adults (18–65 years) with overweight type II (27–29.9 kg/m^2^) or obesity type I (30–34.9 kg/m^2^) will be invited to participate. Interventions will last 17 weeks with follow-ups 1, 3, 6 and 12 months after the post-treatment appointment. The primary outcome will be post-treatment weight loss and the maintenance during the follow-ups. Secondary outcomes will be adherence rates, drop outs and quality of life. Participants will be assessed before randomization and they will be sign an inform consent.

**Discussion:**

The future challenge is to design innovative obesity treatments. Internet could be a useful tool to improve traditional weight control programs. This new intervention format is appropriate for patients who prefer not to share their intimate problems with a group, and for the new generations who feel comfortable using new technologies. Besides, Internet allows reaching a large amount of people at the same time, even if they live far away.

**Trial registration:**

ClinicalTrials.gov NCT04127201. Retrospectively registered 15th October 2019.

## Background

Obesity has become a Western countries public health problem [1]. There was a transition in the last decades and, currently, there are more obese than underweight people over the world [1]. In 2016, according to World Health Organization (WHO), more than 1.9 billion adults were overweight and 650 million of these were obese [2]. People who suffers obesity are more likely to present comorbid diseases like diabetes, cancer or hypertension [3]. Moreover, previous studies have shown an association between obesity and psychological problems like depression, anxiety or stress [4]. Weight discrimination and bias use to be related with psychological problems aforementioned [5, 6].

Obese people need innovative treatment options, previous investigations have developed weight loss programs focused on diet, physical activity and self-recording [7]. These interventions have shown effective short-term weight loss results, but poor adherence rates and long-term results [7–9]. To design effective treatments, it is important to change the focus from treating the problem to treat the person who is suffering the problem, to understand these people and their environment [10].

Traditionally, there was a tendency to blame obese people when they failed or dropped out an intervention [10, 11]. The lack of social support, even by healthcare professionals, is an important barrier to adhere to weight control programs [10, 11]. In general, obese people face an unsupportive environment where the standards of beauty are unrealistic and unreachable, especially for women [12]. The high leisure-time internet use has become another barrier promoting sedentary behaviors [13], and at the same time offering poor quality information about healthy habits to reach the unhealthy thinness ideal [14].

However, internet world usage has grown 1104% since 2000 [15] and, properly-used, could be a potential tool to design innovative interventions [16]. Web-based weight control programs could solve some limitations of traditional interventions. These new tools can reach many people at the same time [17], which is an urgent need [1, 2]. Moreover, the content of these programs must include further areas than nutrition and exercise [7].

Previous reviews have reported effectiveness results of web-based computer-tailored interventions [7–9, 18–20]. These investigations concluded that web-based weight control programs are more effective than control or minimal contact interventions [18, 19]. However, effectiveness results are short-term and adherence is too low comparing with traditional interventions or web-based programs with an extra component, like group reinforcement sessions [7–9, 20]. Web-based interventions with personalized feedback, delivered by a health professional, have reached better results than those without feedback or automatized feedback [9–11]. Therefore, internet could be an innovative and promising way to deliver weight control interventions, but further investigation is need [21].

We have developed a web-based computer-tailored intervention aimed to acquire healthy long-term habits. The body mass index (BMI) of the target population must be between 27 and 34.9 kg/m^2^, namely overweight type II or obesity type I [22]. To design a potentially successful program, basic behavior change aspects have been included: nutrition, physical activity, self-recording and goal setting [7, 23]. Perceived family and friends support were shown particularly helpful during the process of health behavior change [10, 11, 24], and it should be considered during treatment design. Finally, psychological aspects like dealing with negative self-talk must be driven by a healthcare professional, providing personalized feedback and a non-judgmental attitude [9–12]. One of the most tested lifestyle change intervention for weight management is the LEARN program [25]. The word LEARN is an acronym of the five main treatment areas: Lifestyle, Exercise, Attitudes, Relationships and Nutrition [25]. This program is a self-help book which includes basic treatment areas [7, 23], and also includes social support as a relevant aspect to achieve long-term lifestyle changes [10, 11, 24].

However, LEARN program presents two important limitations: i) it is administrated to one person at a time; ii) there is no healthcare professional to solve doubts and provide personalized feedback. Our web-based intervention is an online adaptation of LEARN program [25]. We respected the structure and contents of the original program. However, we adapt the nutrition recommendations to Mediterranean diet, more typical in Spain, and we update the delivery format to reach as many people as possible. In addition to the website, a mobile application was developed to record daily nutrition and exercise information, and weekly weight. To encourage participants a specialized psychologist provides weekly personalized feedback about website activity and mobile application records. This new approach of the LEARN program was named *en_línea.*

In Spain the estimated prevalence of overweight is 39.3 and 21.6% of general obesity in adults between 25 and 64 years old [26]. The main aim of *en_línea* is its application from Spanish primary care centers. Healthcare professionals of primary care centers are the first clinicians to assess and treat obesity [27]. High-intensity in-person interventions in primary care, both individual and group format, have shown effective weight loss results [28, 29]. Unfortunately, the large amount of obesity patients imposes a significant public health expense [30], making impossible to offer quality high-intensity in-person treatment to all affected population. Moreover, these treatment options present a limited reached, people who have to travel great distance to assist to the appointments are likely not to be interested or drop out at early stages [17, 20]. As there are a lot of people in wait lists for obesity treatments in public hospitals and primary care centers, *en_línea* could be a great option for these patients and for those who live away from the assistance centers.

A randomized controlled trial (RCT) is need to examine the effectiveness of *en_línea* comparing with a standard primary care group therapy and a control group. All conditions will be described later in detail. We hypothesize that *en_línea* group will obtain better or, at least, similar effectiveness results than the standard therapy group, and better results than the control group. The primary aim of the RCT will be determine the effectiveness weight loss and maintenance of *en_línea* with the two comparison groups. The secondary objectives to determine the effectiveness of *en_línea* in comparison with the other conditions will be: a) the adherence to intervention, i.e. website tasks and mobile application records; b) number and stage of drop outs. We will conduct a 17 weeks, parallel-group, randomized controlled trial. Randomization will be performed with a simple randomization with a 1:1:1 allocation ratio. The aims of this paper are to describe the development of *en_línea* program and the protocol for the RCT.

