### Outcomes

#### Primary outcomes measures

The primary outcome is the weight loss. First, differences between the pre and post measures for each treatment arm. Treatment success is defined as 5–10% of weight loss respect the initial weight. Then, significant differences in weight loss and other anthropometric measures, specified later, between the three treatment arms. Finally, the maintenance of weight loss during the follow-ups, significant differences between the three treatment arms.

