#### Randomization and blinding

Simple randomization will be applied using computer-generated random numbers [34], with a 1:1:1 allocation ratio. Simple randomization has proven to be reliable to large clinical research, generating similar numbers of subjects per group [34]. Participants will be randomly assigned to *en_línea* program, standard group therapy or control group. Randomization will be carried out by an independent researcher of the study. Therapists will not know the patient allocation until the coordinator inform them to begin the treatment. Thus, blinding will not be possible for the therapists during the intervention.

Currently, this study is in the recruitment phase. No statistical analysis have been performed at this time.

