### Statistical analysis

To estimate the sample size has been used the primary outcome, weight loss differences between baseline and post-treatment measures. The range of the effect size of the intervention will be 0.5 SD in group comparisons, alpha 5% and two-tail tests [51]. These data determine that we need at least 88 patients per group, considering an expected 31% dropout rate [52], our final choice will be *N* = 305 [53].

Analysis will be performed using STATA/IC 14.2. All data will be checked for missing values, accuracy and normality criteria. Intention to treat analysis (ITT) will be used to analyze the data, including all randomized participants. After that, per protocol analysis will be performed for participants who have completed 17 weeks follow-up. ANOVA for repeated measures, with type of intervention as independent variable and time (baseline and follow-up visits) as dependent variable, will be conducted to analyze primary and secondary outcomes.

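### The hypothesis that en_línea is at least similar to group therapy has no margin or criterion; the stated two-sided difference tests can support only the superiority claims

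*Protocol article*

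**What the plan says.** The last paragraph of the Background states the hypothesis: the *en_línea* "group will obtain better or, at least, similar effectiveness results than the standard therapy group, and better results than the control group". It has three limbs: better than group therapy, at least similar to group therapy, and better than control.

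Under Outcomes, Primary outcomes measures, the between-arm criterion is "significant differences in weight loss and other anthropometric measures, specified later, between the three treatment arms". The same kind of criterion is applied to maintenance of weight loss during follow-up.

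The Statistical analysis section sizes the trial on "weight loss differences between baseline and post-treatment measures" and states: "The range of the effect size of the intervention will be 0.5 SD in group comparisons, alpha 5% and two-tail tests". It concludes that "we need at least 88 patients per group, considering an expected 31% dropout rate", and sets a total of N = 305. Allocation is by simple randomization "with a 1:1:1 allocation ratio". The one named analysis is a repeated-measures ANOVA, which "will be conducted to analyze primary and secondary outcomes". It is run by intention to treat (ITT) on all randomized participants and then per protocol.

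The article contains no margin, no definition of similar, no non-inferiority or equivalence test, and no rule based on a confidence interval.

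**The concern.** A test for a difference can show that one arm is better. Failing to find a difference does not show that two arms are alike, because the result depends on precision as much as on the true effect. The hypothesis makes a claim of likeness, while each stated element of sizing and analysis serves superiority.

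This is not a detail that a condensed article may leave to another document. The hypothesis and the basis of the sample size are both printed here, and they do not match. A margin determines how many patients are needed, so it belongs with the design.

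The comparison matters because the Discussion presents *en_línea* as an alternative in primary care. The Background itself reports that adherence to web-based programs is low compared with traditional interventions, so a true deficit against group therapy is plausible.

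**Working it through.** **Inputs.** From the Statistical analysis section: 0.5 SD, two-sided 5%, at least 88 per group, 31% dropout, N = 305. From Randomization and blinding: 1:1:1 allocation. Power is not stated. No margin is stated, so every margin below is an assumption.

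**The plan's own figure.** For 0.5 SD at two-sided 5%, a two-sample t-test needs 64 per arm for 80% power and 86 for 90%. The stated 88 gives 91% power, so it fits a superiority calculation at about 90% power. N = 305 does not follow from 88 and 31% dropout: 3 × 88 = 264, and 264 / (1 − 0.31) = 383. That is a separate matter. It is relevant here only because it leaves the evaluable number uncertain.

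**Evaluable patients per arm (assumed range).**
- 70: 305 × 0.69 / 3 = 70.2, completers at the stated dropout.
- 88: the stated number.
- 102: 305 / 3 = 101.7, all randomized patients.

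**Formulas, in SD units.** The standard error (SE) of a difference between two arms is √(2/n).
- 95% CI half-width = 1.96 × SE. For n = 70: 1.96 × 0.169 = 0.33.
- Chance of a non-significant result at a true deficit d = 1 − power of the two-sided t-test.
- Non-inferiority power (true difference 0, one-sided 2.5%) = Φ(margin/SE − 1.96). For n = 70 and a 0.3 SD margin: Φ(0.3/0.169 − 1.96) = Φ(−0.185) = 43%.
- Margin giving 80% power = (1.96 + 0.84) × SE. For n = 70: 2.80 × 0.169 = 0.47.

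| Evaluable per arm | 70 | 88 | 102 |
|---|---|---|---|
| SE (SD) | 0.169 | 0.151 | 0.140 |
| 95% CI half-width (SD) | 0.33 | 0.30 | 0.27 |
| Non-significant if truly 0.3 SD worse | 58% | 49% | 43% |
| Non-significant if truly 0.5 SD worse | 16% | 9% | 6% |
| Non-inferiority power, 0.3 SD margin | 43% | 51% | 57% |
| Non-inferiority power, 0.5 SD margin | 84% | 91% | 95% |
| Margin giving 80% power (SD) | 0.47 | 0.42 | 0.39 |

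**What a non-significant result can hide.** An observed deficit just under the half-width is non-significant, and its CI then reaches almost twice the half-width: about 0.66, 0.59 and 0.55 SD for 70, 88 and 102 per arm. In each case the interval includes a deficit as large as the 0.5 SD the trial is sized to detect.

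**Size for a chosen margin.** Evaluable patients per arm for 80% power, from n = 2 × ((1.96 + 0.84)/margin)²: 252 for 0.25 SD, 175 for 0.3 SD, 99 for 0.4 SD, 63 for 0.5 SD.

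**The case against.** The strongest reply is that this is a difference-testing trial throughout. Its aim, primary outcome and sizing say so, both superiority limbs are covered by the planned tests, and the problem is one phrase in a Background hypothesis. That is fair as to scope: the superiority comparisons are not affected. But the phrase is part of the stated hypothesis, and nothing in the plan can support it.

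A reader might infer that the plan will treat p > 0.05 as proof of similarity, and so declare a materially worse program similar. The documents do not support that. They state no such rule; they only leave the similarity limb without any other criterion.

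A reader might also infer that *en_línea* is to replace in-person therapy on the strength of this comparison. The Background and Discussion aim it mainly at people waiting for treatment or living far from it, for whom the comparison with control matters at least as much.

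Nor can it be said that more dropout must make a non-significant result more likely under ITT. That depends on how missing weights are handled, which the article does not state.

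Finally, 70 per arm is the least favourable case, since the document states at least 88 per group and an ITT set of about 102 per arm. The problem is smaller at those numbers but remains. A CI from the same data could support non-inferiority against a preset margin, which is the first option under the fix.

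**Conclusion.** The concern holds as a mismatch between a stated hypothesis and the stated analysis. The plan can support the superiority limbs but not the similarity limb. Across 70 to 102 evaluable patients per arm, a true 0.3 SD deficit would go undetected 58% to 43% of the time. Non-inferiority power at an assumed 0.3 SD margin would be 43% to 57%. A margin of 0.47 to 0.39 SD would be needed for 80% power, which is most of the 0.5 SD effect the trial is sized to detect. These figures assume equal arms, a simple two-arm comparison of week-17 weight loss and, for the non-inferiority power, no true difference. The margins are illustrative. The conclusion that the similarity limb has no test does not depend on any of these figures.

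**What to change.** The article says the study is still recruiting and nothing has been analysed, so either option can be adopted before data are seen.

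**(a) Keep the claim and give it a test.** Set a margin in kg for the week-17 difference in weight loss between *en_línea* and group therapy, justified on clinical grounds. Conclude similarity (non-inferiority) only if the two-sided 95% CI excludes a deficit as large as that margin in both the ITT and per-protocol sets. Read superiority from the same CI. State the power that the planned N gives for that margin. The document gives no SD in kg, so the value assumed must be stated. The margin should come first and the power follow from it; the 0.39 to 0.47 SD above is not a criterion for an acceptable margin. If the power is inadequate, the choice is to re-size or to take option (b). Requiring success in both sets lowers power further, by an amount not computed here.

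**(b) Drop the claim.** Delete the similarity wording from the hypothesis, report the difference with its 95% CI, and state that a non-significant result is not evidence of similarity.

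**Cost.** Option (b) is a change of wording and needs no extra patients. Option (a) needs a justified margin and possibly a larger trial. The similarity claim becomes harder to make under (a) and is given up under (b).

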## Methods/design

This protocol is written according to SPIRIT 2013 guidance for protocols of clinical trials (Fig. 1) [31].

**Fig. 1 Fig1:**
[figure not shown]
Overview of research schedule and procedure

### Setting

The study will be conducted at the Unit of Behavior Therapy, a clinic service in the Faculty of Psychology of the University of Barcelona, located in Barcelona. The center is registered in the Sanitary Registration of the Health Department of the Government of Catalonia. The Unit of Behavior Therapy was opened in 1985 to provide psychological service to the community and to train new psychologists [32]. Currently, the center is staffed by psychologists in training, two supervisors and four experience psychologist. The clinic service director is a clinical psychologist expert in the study and treatment of eating disorders and obesity.

### Participants

The target population will be overweight type II or obese type I people, from the community and from the metropolitan area of Barcelona and surroundings. Participants are volunteers and they must sign the written informed consent before beginning with the investigation procedures.

#### Inclusion criteria

At randomization, eligible participants for the trial must comply all following requirements: 1) Overweight type II or obesity type I. BMI between 27 and 34.9 kg/m^2^; 2) Age between 18 and 65 years old; and, 3) Compliance with all evaluation phases.

#### Exclusion criteria

If eligible participants present at least one of the following criteria, they will be excluded from the trial: 1) Presence of several physical disease, i.e. diabetes, hypertension, cancer or metabolic disorders; 2) Presence of several psychological problem, i.e. depression, anxiety; 3) Presence of other eating disorders, i.e. anorexia nervosa, bulimia nervosa, binge eating disorders; 4) Use of drugs, i.e. slimming, anovulatory or psychotropic; 5) Pregnancy or planned pregnancy for the next 6 months; and, 6) Following another weight control program at the time of selection.

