#### Control group

Participants in the control group only will receive a biweekly newsletter by email without feedback. They will be provided with material and instructions to self-record their daily meals and exercise. The newsletter only will content basic information about nutrition and exercise.

Follow-up sessions will take place in three arms to assess the adherence to the interventions and to evaluate the main objective of this study, the acquirement of long-term healthy habits. These face-to-face sessions will last between 15 and 30 min and will take place 1, 3, 6 and 12 months after the post treatment session. In this follow-ups, we will review: anthropometric measures, quality of life, nutrition and exercise habits.

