### Study design and randomization

#### Procedure

Participants will be recruited through advertising (flyers, posters, University website, workplace-based emails and social networks). Obese and overweight people interested in participating in the study must send an email to the coordinator of the project. Participants will receive an email to attend an appointment with a psychologist. In this first appointment, patients will be informed about the aims and characteristics of the study, they must sign the written informed consent and, after that, a brief interview and baseline anthropometric measures will be taken. Anthropometric measures will be weight, height; and, neck, chest, waist, hips, leg and arm circumferences. All measures will be taken with the participant wearing light clothing and without shoes. Height will be taken with 1 cm using a stadiometer. Weight will be measured on a digital scale. Circumferences measurements will be measure following the indications provided by WHO [33].

To ensure the accomplishment of inclusion and exclusion criteria participants must answer a large battery of questionnaires specified later. These questionnaires are divided in two batches. After the first in-person appointment, participants will receive an email with the instructions to complete the first batch of questionnaires, they will be provided with an identity number for data protection and with the direct link to the available questionnaires in the platform SurveyMonkey. After the completion of the first part, a second email with the link to the second batch of questionnaires will be sent.

Assessment phase will last 2 weeks, selected participants will be randomized to one of the three study arms. Patients will receive an email with information about their belonging group. Obese and overweight people randomized to *“en_línea”* program, must assist to a 1 h training session to get familiar with the website and the mobile application. When participants are included in the study, both *en_línea* and group intervention, they will be given timings for follow-up meetings during the treatment at week 8 and week 17. After interventions finish, follow-up meetings will be happened at 1, 3, 6 and 12 months. In the follow-up visits a brief interview and anthropometric measures will be taken again, the duration of these meeting will be between 15 and 30 min (Fig. 3).

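### The planned-pregnancy exclusion looks 6 months ahead, but maintenance of weight loss is measured to about 16 months, so 6-month and especially 12-month follow-up weights can be affected by pregnancy

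*Protocol article*

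**What the plan says.** All references are to the Protocol article.

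- **Eligibility.** Exclusion criterion 5 is "Pregnancy or planned pregnancy for the next 6 months". Adults aged 18 to 65 can enter. Criterion 4 in the same list is "Use of drugs, i.e. slimming, anovulatory or psychotropic".
- **Timing.** The Abstract (Methods) states: "Interventions will last 17 weeks with follow-ups 1, 3, 6 and 12 months after the post-treatment appointment". The Control group section says of all three arms that the face-to-face follow-ups "will take place 1, 3, 6 and 12 months after the post treatment session". Procedure places a step before randomization: "Assessment phase will last 2 weeks".
- **What is measured.** Procedure says: "In the follow-up visits a brief interview and anthropometric measures will be taken again". These measures are weight and a set of circumferences that includes waist and hips.
- **What it is used for.** Primary outcomes measures ends with: "Finally, the maintenance of weight loss during the follow-ups, significant differences between the three treatment arms".
- **Analysis.** Statistical analysis specifies intention to treat with everyone randomized, then a repeated-measures ANOVA with baseline and the follow-up visits as time points. The sample size rests on weight change from baseline to post-treatment.

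**The concern.** The authors exclude women who are pregnant or plan to be, but the stated horizon is much shorter than the period over which weight is an outcome. A woman who truthfully says she intends to conceive in, say, month 7 meets the criteria. Her later weights and circumferences then enter the maintenance comparison, where weight gained in pregnancy looks the same as failure to maintain the loss.

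At stake is the long-term part of the primary outcome. The article names poor long-term results as a limitation of existing programmes that this trial should overcome. A few large gains unrelated to treatment add variance. If they fall unevenly across arms by chance, they also move the arm means. Waist circumference is especially exposed.

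**Working it through.** **Step 1. Visit calendar.** Inputs: 17 weeks of treatment, follow-ups at 1, 3, 6 and 12 months, and a 2-week assessment phase. The article does not say from which day the 6 months run, so both origins are shown. One month = 365.25/12 = 30.44 days.

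- Treatment: 17 × 7 / 30.44 = 3.91 months
- Assessment: 14 / 30.44 = 0.46 months

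| Visit | Months from randomization | Months from start of assessment | Inside the 6-month window? |
|---|---|---|---|
| Post-treatment | 3.9 | 4.4 | yes |
| 1-month | 4.9 | 5.4 | yes |
| 3-month | 6.9 | 7.4 | no |
| 6-month | 9.9 | 10.4 | no |
| 12-month | 15.9 | 16.4 | no |

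From either origin the window closes between the 1-month and 3-month visits. It covers 6/15.9 = 38% (6/16.4 = 37%) of the observation period and leaves 9.9 (10.4) months uncovered.

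**Step 2. What each later weight can be.** Take the earliest conception that the criterion permits, immediately after month 6. Assume 266 days (38 weeks) from conception to birth; this figure is not in the article. Maximum time since conception, with the assessment origin in brackets:

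- 3-month visit: 0.91 × 30.44 / 7 = 4 weeks (6 weeks)
- 6-month visit: 3.91 × 30.44 / 7 = 17 weeks (19 weeks)
- 12-month visit: 9.91 × 30.44 / 7 = 43 weeks (45 weeks), which is up to 43 − 38 = 5 (45 − 38 = 7) weeks after birth

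So the 3-month weight can only be a very early pregnancy weight. The 6-month weight can be a pregnancy weight up to 17 to 19 weeks after conception. The 12-month weight can be from any stage of pregnancy or early post-partum.

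**Step 3. How many women (illustration only).** The article gives no sex mix and no pregnancy rate. Assume 50 to 85% women, 40 to 60% of them of childbearing age, and 3 to 8 pregnancies per 100 woman-years over 10.4 uncovered months:

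- Low: 305 × 0.50 × 0.40 × 0.03 × 10.4/12 = 1.6
- Central: 305 × 0.70 × 0.50 × 0.05 × 10.4/12 = 4.6
- High: 305 × 0.85 × 0.60 × 0.08 × 10.4/12 = 10.8

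These counts refer to everyone randomized. With the article's 31% dropout, multiply by 0.69: 1.1, 3.2 and 7.4 among those still observed. The central value is about 3.2/3 = 1 per arm. The assumed rate mixes planned and unplanned pregnancies, so it overstates what a longer window could prevent.

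**Step 4. Effect on an arm (upper-end case).** Observed per arm: 305 × 0.69 / 3 = 70. Assume two pregnancies in one arm and none in the others, 10 kg each, and an SD of 5 kg otherwise:

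- Mean shift: 2/70 × 10 = 0.29 kg
- SD: √(25 + (2/70)(68/70) × 100) = √27.8 = 5.3 kg, about 5% higher
- Against the planned difference of 0.5 SD = 2.5 kg: 0.29/2.5 = 11%

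This leans high. A gain of 10 kg belongs to late pregnancy. If conceptions spread evenly over the 45 uncovered weeks, about 12/45, roughly a quarter, would be in the last 12 weeks of pregnancy at the 12-month visit. About another quarter would be in the first 12 weeks after conception.

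**The case against.** The other side has a fair case.

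- **The window fits the comparison that sizes the trial.** It covers assessment, all 17 treatment weeks, the post-treatment weight and the 1-month weight. This stands: that comparison is not touched by any pregnancy the criterion lets through. But maintenance is also named as part of the primary outcome, so the later visits cannot be set aside.
- **Intentions stated 16 months ahead are a weak screen, and no window stops unplanned pregnancy.** This also stands. It means that changing the criterion is not enough by itself; it does not justify the present mismatch.
- **Randomization gives no reason to expect pregnancies to cluster in one arm.** True. The expected result is extra variance and a chance imbalance, not a systematic bias.

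A reader might also infer more than the article supports:

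- *That the 3-, 6- and 12-month weights are all exposed to pregnancy or post-partum change.* The calendar does not allow it. The 3-month weight is at most 4 to 6 weeks after conception, and only the 12-month weight can be post-partum.
- *That the plan is wrong because it has no rule for weights taken in pregnancy.* A journal article commonly leaves such data handling to the full protocol or analysis plan, which are not shown. The point rests only on the stated window against the stated follow-up.
- *That excluding users of anovulatory drugs raises the pregnancy rate.* It may shift enrolment away from hormonal contraception, but the article says nothing about other methods. This is possible, not shown.

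**Conclusion.** The mismatch is real and follows from the article's own figures: a 6-month horizon against 15.9 to 16.4 months of weight measurement, with three of four follow-up visits beyond it. In practice it concerns the 12-month weights and circumferences and, to a lesser degree, those at 6 months. The 3-month visit is little affected and the post-treatment comparison is not affected.

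The size cannot be computed from the article. Under the assumptions shown, a few participants would be involved, and 0.29 kg in one arm is an upper-end illustration rather than an estimate. It would be tempting to conclude that the maintenance result is materially biased; nothing in the article establishes that. Confidence is high for the calendar and low for the consequence. This is a cheap improvement of low-to-moderate priority.

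**What to change.** 1. **Eligibility.** Reconcile the planned-pregnancy window in the Exclusion criteria with the 12-month follow-up, for participants not yet enrolled.
2. **Data collection.** Ask about pregnancy and recent birth at each follow-up interview already planned. This reaches people enrolled under the present criterion as well as unplanned pregnancies.
3. **Analysis.** If the full protocol or analysis plan does not already do so, prespecify that weights and circumferences taken during pregnancy, or within a stated post-partum period, are not used as maintenance outcomes. Treat them as missing in the main analysis and include them in a sensitivity analysis.

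The Randomization and blinding section says that recruitment is under way and no analysis has been done, so the rule can still be set in advance.

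Cost: one eligibility line, one interview question and one analysis sentence. Downside: a few eligible women lost to recruitment, and a few late weights missing from the main analysis.
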